### 6.2.1 Inclusion Criteria

Vulnerable, pregnant Australian women, who have sufficient English proficiency to answer questions face-to-face. The inclusion criteria, based on the results of our pilot (RCH HREC 32771, Northern Health HREC P 20/12), are any two of the following 10 risk factors:

- Current smoking,
- Young pregnancy (<23 years old),
- No support (emotional, financial, practical) during pregnancy,
- Poor/fair/good general health (versus very good/excellent general health)
- Anxious mood,
- Not finishing high school,
- Not having a household income,
- A long-term illness,
- Living without another adult, and
- Never had a job.

### **6.2.2 Exclusion Criteria**

Women will be excluded if:

- Their child is removed from the home during the course of the research such that they are ineligible for the trial. If it emerges that child is being removed from his/her home (i.e. intervention nurses inform the study team, or a researcher phone call to the mother to schedule an assessment reveals it), then the CIs [name] and [name] will consider whether the family can remain in the trial on a case-by-case basis. Remaining in the trial will depend on the length of time the child is removed from the home, as it is not possible to assess the effectiveness of an intervention if the family has no access to the intervention or usual care alternative. In some cases, it will only be possible to consider full exclusion of a family at the end of the trial.
- They are enrolled in the Victorian Department of Human Services 'Cradle to Kinder' research program
- They are enrolled in the Tasmanian Department of Health and Human Services CU@home home visiting program
- Do not comprehend the recruitment invitation (e.g. have an intellectual disability such that they are unable to consent to entering the study, or have insufficient English to complete face-to-face assessments, i.e. require an interpreter)
- Have no mechanism for contact (landline or mobile telephone, or email address)
- Experience a critical event such as miscarriage, late termination of pregnancy, stillbirth and neonatal death.

### **6.3 Randomisation Procedures**

Patients will be randomly assigned to receive the treatment (home visiting intervention) or usual care arms. Families will be equally divided between the two arms, based on our sample size estimation (see Section 10.1). A statistician not directly involved in the analysis of the study results

will prepare the randomisation schedule using block randomisation to maintain balance between treatment arms. Randomisation will be stratified both by parity (1st time parent vs. those with children already) and site. The schedule will be administered using a web-based randomisation schedule to enable randomisation to be conducted remotely at each location. Sealed envelopes containing randomised treatment allocation will be provided to each study location in case of the event that the web based system cannot be accessed during the randomisation of a participant.

#### **6.4 Blinding Arrangements**

The project manager, participants and nurses will be aware of the allocation to treatment arm to enable organisation for the mothers to receive the active or control intervention. Research staff responsible for conducting outcome assessments will be blinded to treatment allocation. Families will be asked not to disclose their randomisation status at assessments; however, those that do will be recorded in the study database and this 'unbinding' will be examined as a potential confounding variable in the outcome analyses.

#### **6.5 Breaking Of The Study Blind**

##### **6.5.1 On Study**

Breaking of the study blind is not applicable as the study coordinator, mothers and nurses are aware of the allocation.

##### **6.5.2 Following Completion of the Study**

Research staff and the statistician responsible for the study analysis will be supplied with the treatment allocation for each participant when all mothers and children have completed the primary outcome assessment at 24 months.

#### **6.6 Subject Withdrawal**

##### **6.6.1 Reasons for withdrawal**

The research team may withdraw a participant from the study treatment and follow-up procedures if the participant:

- Is in violation of the protocol
- Experiences a serious or intolerable adverse event
- Develops, during the course of the study, symptoms or conditions listed in the exclusion criteria
- Requires early discontinuation for any reason
- Experiences a critical event such as miscarriage, late termination of pregnancy, stillbirth and neonatal death.

The latter will be identified via the research phone calls made throughout the study. We understand that it may be extremely difficult for women to share this information, so phone calls will be

conducted using the same sensitive procedure employed in other studies conducted at the MCRI. The researcher will begin the conversation by asking the mother how she is, which allows the mother to volunteer the information. For mothers in the intervention arm, intervention nurses are likely to learn of these events before the researcher. Intervention nurses will then pass this information back to the research CIs, and one of the CIs will contact the parent to express their sadness, take them off the database, and offer the maternal and child health service number in case parents want additional support. For control participants, the researcher conducting the phone call (CI [name] or RO [name]) will offer the same information, and ask whether the mother would like CI [name] to contact their maternal and child health nurse to request more support.

At enrolment, women will be given study details on the PIS&C, and invited to contact the study team with any details they think we should know about. These processes have worked well in other MCRI studies.

The research team will withdraw all participants from the study treatment if the study is terminated. Patients are free to withdraw from the study at any time upon their request or the request of their legally acceptable representative.

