## **5.2 Measurement of subject compliance**

Subject compliance will be measured with fidelity instruments completed at every home visit, which are yet to be finalised but will be based on those used for MESCH (see **Appendix 8** and **Appendix 9** for antenatal and postnatal checklists, respectively). The checklists are used to record intervention delivery and fidelity only, and will not be seen by researchers assessing families. We will submit the fidelity measures for ethical approval once finalised for right@home. Significant non-compliance is defined as missing 6 months of the program, i.e. if no attendance for 6 months.

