#### **6.6.2 Handling of withdrawals and losses to follow-up**

If the participant is withdrawing from the intervention, the research team will ask whether they are still happy to take part in the research assessments in an effort to maintain the intention-to-treat analysis. If the participant withdraws fully from the study, they will cease to undergo scheduled assessments. Participants will be asked (only if willing) to share the reason for ceasing the intervention or participation in the full trial. Reasons will be recorded by the research team in the study database. Where it is not possible to contact a family, a limited number of follow-up processes will be conducted, including:

- (1) 2 documented phone calls including alternative assessment settings offered,
- (2) 2 documented emails (where email address are provided),
- (3) Contacting Centrelink for updated contact details where consent to record the family's Centrelink is obtained. We are currently making inquiries into whether this is possible and will only be able to do it with the correct authority.

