Where the incident occurs during a researcher visit, we will follow the processes used successfully in MECSH. For psychosocial and drug/alcohol problems, researchers will recommend that women phone the maternal and child health line ([name]). They will also ask if the woman would like CI [name] to phone and offer a more specific referral. For domestic violence and child abuse/neglect problems, researchers will report using the local public child protection system, i.e. via the usual public child protection helpline ([name]). Researchers with concerns will be asked to discuss, in the first instance, the child protection issue with CI [name] (see details in the Safety and Communication Protocol, Appendix 21). While researchers are not mandatory reporters, CI [name] is. The research team will follow-up as required based on the response from the child protection system. The research staff will also be provided with support and debriefing from CIs and MCRI counselling.

Changes in the severity of an AE will be reported. AEs characterized as intermittent will be documented for each episode. All AEs will be followed to adequate resolution, where possible.

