We acknowledge that our choice of a 40% attrition rate is lower than the attrition in MECOSH (45% participated in 2 year follow-up in the control arm compared with 57% in the intervention arm). This is for two reasons. First, in MECOSH, participants were lost to follow-up if they changed addresses out of the single Sydney suburb that the trial was conducted in. We expect the right@home families to be equally transient, but the nurses and researchers can still reach them if they live in the same region. There is also the possibility that families could swap nurses if they move out of one right@home region and into another, and this will be organised if and when cases arise. As such, we are confident that we will lose fewer families to itinerancy. Second, according to [name], part of the MECOSH attrition was due to families not being high-risk enough to benefit from the program and feeling that they did not need the information. This is supported by the home visiting literature which suggests that the most vulnerable families benefit most from the interventions. For this reason, right@home aims to recruit only the most vulnerable families (i.e. ~5% rather than ~15% in MECOSH).

We acknowledge that differential attrition, as evident in the MECOSH follow-up, is a significant risk. The primary reason for the follow-up phone calls to all families at 6 weeks, 6 and 18 months is to maintain contact. The secondary reason is to collect data so that the burden of the face-to-face assessments is reduced. We will contact the right@home nurses and maternal and child health nurses responsible for the usual care families for contact details when we lose contact. If it is

possible, we will obtain consent to record the family's Centrelink number so that we can obtain current contact details if we lose contact with the family. We are currently making inquiries into whether this is possible and will only be able to do it with the correct authority and ethical approval.

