## **10.2 Population to be analysed**

The intention-to-treat population will be used in the analyses. Mothers (and children) will be compared according to the group to which they were randomly allocated, regardless of mothers' compliance, crossover to other treatments or withdrawal from the study. This approach preserves the prognostic balance in the study arms achieved by randomisation.

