## **10.3 Statistical Analysis Plan**

The frequency and patterns of missing data will be examined and sensitivity analyses will be performed comparing the results of analyses restricted to families with complete data and analyses where missing data are imputed using a conservative approach.

The baseline characteristics of the mothers will be presented for each treatment arm using the mean, median and IQR for continuous data and proportions for categorical data. Maternal and child outcome measures will be similarly described by treatment arm and comparisons made using the t-test and non-parametric tests for continuous data and the chi-squared test for categorical data.

Linear and logistic regression modelling will be conducted to test the primary and secondary hypotheses listed below, taking into account maternal baseline and child characteristics identified *a priori* i.e. child gender, socio-demographic characteristics of the mother and family, and maternal specific characteristics including health, mental health and self efficacy.

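### Section 6.6.1 lets the research team end follow-up, not only the program, on three grounds that usually leave a 2-year assessment possible; limiting the rule to the program is a cheap improvement

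*Protocol*

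**What the plan says.** Section 6.6.1 gives the team one discretionary power over two things, the program and the assessments: "The research team may withdraw a participant from the study treatment and follow-up procedures if the participant" meets a listed condition. This point concerns three of the conditions: violation of the protocol, a serious or intolerable adverse event, and "Requires early discontinuation for any reason". The critical-event and exclusion-criteria grounds in the same list are outside it, as is the possible exclusion in section 6.2 of women who do not need the program.

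Section 6.6.2 contains the only offer of continued assessment: "If the participant is withdrawing from the intervention, the research team will ask whether they are still happy to take part" in the research assessments. Its stated purpose is to protect the intention-to-treat analysis. A participant who leaves fully has no further scheduled assessments. Section 6.6.3 rules out replacement and points to the 40% attrition allowance.

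Section 10.2 compares mothers as randomised, "regardless of mothers' compliance, crossover to other treatments or withdrawal from the study". Section 10.3 plans a sensitivity comparison of complete-data results with "analyses where missing data are imputed using a conservative approach". Section 10.1 states: "We acknowledge that differential attrition, as evident in the MECOSH follow-up, is a significant risk".

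**The concern.** An intention-to-treat comparison needs the 2-year outcome of every randomised mother from whom it can be obtained. A protocol violation, a hospital admission (which section 9.1 counts as serious) or an unspecified reason may justify stopping the visits. None of them usually stops a researcher from assessing the family at 2 years. A rule that ends both together turns a treatment decision into missing outcome data.

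This is a matter of what the protocol states, not of detail left to an analysis plan. No analysis plan can restore an assessment that the team cancelled. For these three grounds the protocol also names neither a criterion nor a decision-maker, whereas section 6.2.2 gives child-removal cases to named investigators, case by case.

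Equal removal of similar mothers in both arms would cost only precision. Removal related to outcome and unequal between arms would bias the primary comparisons.

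**Working it through.** **1. The texts side by side**

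| Question | Section | Answer |
|---|---|---|
| May the team end follow-up? | 6.6.1 | Yes, at its discretion |
| Must it do so on these grounds? | 6.6.1 | No |
| Is continued assessment offered? | 6.6.2 | Yes, to a participant who is withdrawing from the intervention |
| Does that offer limit the team's power? | 6.6.2 | Not stated |
| Is a 2-year outcome still obtainable? | 9.1 | Usually; not after death, which is one of the serious-event criteria |
| Are earlier measures available? | Table 4 | Parent care, responsivity, CHAOS and HOME at 1 year; the language inventory at 2 years only |

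**2. The plan's own sample size**

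Inputs from section 10.1: 400 per arm, 60% retention, intra-class correlation 0.02, cluster size 29, difference 0.315 SD, power 80%. Two-sided alpha of 0.05 is assumed because none is stated.

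- Design effect = 1 + (29 − 1) × 0.02 = 1.56.
- Assessed per arm = 400 × 0.60 = 240. Effective number = 240 / 1.56 = 153.8.
- Power at 0.315 SD = 78.9%; difference detectable with 80% power = 0.319 SD.

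This agrees with the stated figures to within rounding. Below, the plan's own 80% at 0.315 SD is the starting point.

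**3. Precision, if removals are equal and come on top of the allowance**

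The removal fraction p is assumed, since the protocol gives none. So is q, the chance that a removed mother would have been lost anyway: 0.40 (as planned for everyone) or 0.80. Assessments lost per arm = 400 × p × (1 − q). Detectable difference = 0.315 × √(240/n), with the design effect held fixed.

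| p | q | Lost | n | Detectable (SD) | Power at 0.315 SD |
|---|---|---|---|---|---|
| 5% | 0.80 | 4 | 236 | 0.318 | 79.3% |
| 5% | 0.40 | 12 | 228 | 0.323 | 78.0% |
| 10% | 0.80 | 8 | 232 | 0.320 | 78.7% |
| 10% | 0.40 | 24 | 216 | 0.332 | 75.7% |

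If the design effect falls with cluster size (14 nurses), the detectable differences are 0.317, 0.321, 0.319 and 0.328 SD. If removals fall within the 40% allowance, there is no loss against plan.

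**4. Bias, if removals were unequal and outcome-related**

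This is a what-if; neither condition is shown. Let removed families score d SD below their arm's mean. With the rule, the mean among those assessed is p·d/(1 − p). Without it, the mean is p·d·[0.6 − (1 − q)] / [p(1 − q) + 0.6(1 − p)]. The shift in an arm is the first minus the second. Take d = 1, or d = φ(z_p)/p if the removed families are exactly the worst scorers.

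Example with d = 1 and q = 0.40: the second term is zero, so 5% against 2% gives 0.05/0.95 − 0.02/0.98 = 0.053 − 0.020 = 0.032 SD.

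| Removal by arm | q | d = 1 | Worst scorers |
|---|---|---|---|
| 5% vs 2% | 0.40 | 0.032 | 0.059 |
| 5% vs 2% | 0.80 | 0.011 | 0.021 |
| 10% vs 5% | 0.40 | 0.058 | 0.086 |
| 10% vs 5% | 0.80 | 0.022 | 0.032 |

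The range of 0.011 to 0.086 SD is about 4% to 27% of 0.315. It halves (0.006 to 0.043 SD) if the baseline covariates in section 10.3 explain half of the deficit. It is zero at 5% vs 5%, and it changes sign if the control arm loses more.

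**The case against.** The rest of the protocol leans towards keeping mothers in. Section 6.6.2 follows directly on the list of reasons and aims to protect the intention-to-treat analysis, so treating team-ended cases as outside it is a narrow reading. Section 5.2 attaches no removal to poor attendance: "Significant non-compliance is defined as missing 6 months of the program", and nothing follows from that. Section 9.2 says: "All AEs will be followed to adequate resolution, where possible". Section 12.4 has deviations assessed and reported. All this makes frequent use of the power unlikely. It does not withdraw the power, which expressly reaches follow-up.

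Three further objections stand and limit the point:

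- **Not every case leaves an outcome to collect.** Serious events include death, so a reader who infers that none of the three grounds can prevent a 2-year assessment goes too far.
- **The losses may already be budgeted.** Section 6.6.3 does not separate discontinuation by the team from discontinuation by the mother. A reader might add these losses to the 40%, but the text does not establish that.
- **Imputation is not helpless.** The 1-year measures in Table 4 can inform it for mothers removed after that visit. They cannot do so for earlier removals or fully replace a 2-year observation.

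Some discretion over follow-up is also right: section 9.1 recognises that questions may distress and that taking part may cause family conflict.

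**Conclusion.** The point holds as a rule that permits avoidable missing data and works against the protocol's own aim in section 6.6.2 and the comparison in section 10.2. It is a cheap improvement, not a demonstrated flaw in the results.

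A reader might infer that the primary comparisons would be biased. Section 9.2 lists home safety and child protection among the most likely adverse events, home safety is part of the first primary outcome (Table 2), and the nurses' visits might bring more events to light in the intervention arm. The documents do not support that inference. Section 9.2 answers such events with reporting, referral and follow-up, not removal, and nothing shows that removals would differ by arm or relate to outcome. The direction of any bias cannot be predicted either.

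The size is unknown because no removal rate is given, and it is probably small. All the illustrative figures rest on assumed rates; the precision losses also assume removals beyond the 40% allowance.

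**What to change.** In section 6.6.1, for these three grounds, let the team end study treatment only. Keep the mother on the assessment schedule to 2 years unless:

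- she withdraws consent;
- the assessments themselves are judged harmful to her; or
- the outcome cannot be obtained, because of a critical event or the death of mother or child at any time.

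In section 6.6.2, state that the offer of continued assessment also covers a mother whose program the team ends.

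The cost is one wording amendment and a few assessments of families already in the budget. Some team judgement remains, for harmful assessments, and that is appropriate.

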#### **6.6.2 Handling of withdrawals and losses to follow-up**

If the participant is withdrawing from the intervention, the research team will ask whether they are still happy to take part in the research assessments in an effort to maintain the intention-to-treat analysis. If the participant withdraws fully from the study, they will cease to undergo scheduled assessments. Participants will be asked (only if willing) to share the reason for ceasing the intervention or participation in the full trial. Reasons will be recorded by the research team in the study database. Where it is not possible to contact a family, a limited number of follow-up processes will be conducted, including:

- (1) 2 documented phone calls including alternative assessment settings offered,
- (2) 2 documented emails (where email address are provided),
- (3) Contacting Centrelink for updated contact details where consent to record the family's Centrelink is obtained. We are currently making inquiries into whether this is possible and will only be able to do it with the correct authority.

#### **6.6.3 Replacements**

Patients who discontinue the study will not be replaced by further recruitment to maintain the required sample size. Based on attrition data from previous home visiting randomised controlled trials, our sample size estimation (Section 10.1) has allowed for a potential attrition of 40% at 2 years.

### **6.7 Trial Closure**

There are no circumstances under which the study will be terminated prematurely. The study may be extended if the recruitment rate is slower than anticipated and it is necessary to lengthen the recruitment period to reach the necessary sample size. In addition, we may extend the trial to follow-up the cohort until school age (5-6 years), to assess the effects of the home visiting

intervention on children's early learning and development. Extending the trial to assessments beyond age 2 years will depend on the success of future grant applications. We will seek participant consent for contact for these follow-ups and potential data linkage in future ethics modifications.

## **6.8 Continuation of Therapy**

The home visiting intervention will not be offered to participants beyond the child's second birthday.

## **7. STUDY VISITS AND PROCEDURES SCHEDULE**

The Study diagram in Section 4.2 and Figure 3 below depict the study visits schedule. From April 2013 to March 2014, researchers will approach women at antenatal clinics listed in Section 1.1 to invite women to take part in the screening survey (**Appendix 15**). At this point, consent involves agreeing to complete the screening survey and, if eligible, being invited into the right@home trial. Researchers will then visit interested and eligible women in their homes within 1-2 weeks of the initial screening procedure, to tell them more about the right@home study, and collect informed consent for participation in the randomised controlled trial and a thorough baseline assessment.

Once women complete the baseline assessment, they will be randomised into one of the intervention or usual care arms. Whether this randomisation takes place in the woman's home (at the end of the enrolment visit) or over the phone will depend on whether the intended electronic data collection processes can incorporate the web-based randomisation program, and whether the tablets can connect via 3G/wireless internet. Once a woman is randomised, her details will be sent to the right@home nurse coordinator responsible for that region, and the nurse will be responsible for initiating contact and beginning the intervention. Follow-up assessments will be conducted by the research team via phone at 6 weeks, 6 months and 18 months postpartum, and via face-to-face home visits at 12 and (the final follow-up at) 24 months.

Due to the anticipated low literacy level of the participant group, we are designing all assessments so that they can be completed face-to-face by interview. Responses will be recorded by researchers electronically on tablets, except for some sensitive questions (highlighted in the questionnaire), where the participant will be given the option to complete by themselves either by reading it or having it read to them.

**Figure 5: Graphical depiction ('Perera diagram') of the components of the trial shared and unique to the intervention and control groups**

| Time point relative to randomisation                | Intervention                                                                                                             | Control |
|-----------------------------------------------------|--------------------------------------------------------------------------------------------------------------------------|---------|
| Screening (face-to-face)                            |                                                                                                                          | A       |
| Informed consent (face-to-face)                     |                                                                                                                          | B       |
| Enrolment & Baseline Data Collection (face-to-face) |                                                                                                                          | C       |
| Randomisation                                       |                                                                                                                          |         |
| SNHV                                                | D                                                                                                                        |         |
| 6 week phone assessment                             | E                                                                                                                        | E       |
| SNHV                                                | D                                                                                                                        |         |
| 6 month phone assessment                            | F                                                                                                                        | F       |
| SNHV                                                | D                                                                                                                        |         |
| 1 year face-to-face assessment                      | G                                                                                                                        | G       |
| SNHV                                                | D                                                                                                                        |         |
| 18 month phone assessment                           | H                                                                                                                        | H       |
| SNHV                                                | D                                                                                                                        |         |
| 2 year face-to-face assessment                      | I                                                                                                                        | I       |
| A                                                   | Screening survey for pregnant women in antenatal clinics                                                                 |         |
| B                                                   | Women who meet the eligibility criteria and are interested in the RCT are visited in their home to obtain formal consent |         |
| C                                                   | After obtaining formal consent, eligible women will complete a baseline questionnaire                                    |         |
| D                                                   | Sustained nurse home visiting intervention                                                                               |         |
| E                                                   | Study 6 week follow-up to assess pregnancy, health care access and health literacy                                       |         |
| F                                                   | Study 6 month follow-up to collect new contact details, health literacy and health service use data                      |         |
| G                                                   | Study 1 year follow-up to assess primary and secondary outcomes                                                          |         |
| H                                                   | Study 18 month follow-up to collect new contact details, health literacy and health service use data                     |         |
| I                                                   | Study 2 year follow-up to assess primary and secondary outcomes                                                          |         |

The schedule for collecting primary and secondary outcomes is presented in Table 4 below. These were previously described in Section 4.5. Additional details about these measures and their psychometric properties are provided in Appendix 4.

